### Interventions

#### Intervention Plan

Upon admission, nurses provide admission education and assign eligible patients to the study group or the control group based on the time of admission (Figure 1). The intervention plans for both groups are outlined in a pathway form and include 3 components: executing medical orders, nursing tasks, and health education, along with TCM-specific treatments (Multimedia Appendix 1). For the control group, nurses subjectively implement the nursing plan according to the pathway form. The study group strictly follows the TCM nursing pathway for T2DM.

**Figure 1 figure1:**
[figure not shown]
Study design and flow.

#### Implementation of the TCM Nursing Pathway for T2DM

Upon admission, nurses provide admission education and assess the patient’s condition using an evaluation form for the TCM nursing pathway for T2DM. This assessment determines whether the patient qualifies for inclusion in the study. Eligible patients receive the TCM nursing pathway for T2DM. For patients included in the study, nurses ensure that physicians perform a thorough examination upon admission. The TCM nursing pathway form for T2DM is distributed, and patients are informed about their treatment and the nursing plan during hospitalization. This ensures patients understand the medical and nursing measures to be implemented.

During hospitalization, the responsible nurse uses the evaluation form of the TCM nursing pathway for T2DM to develop an appropriate care plan. This plan may include TCM techniques, syndrome differentiation–based dietary therapy, exercise and health practices, herbal prescriptions, and emotional regulation. The study group strictly adheres to the schedule outlined in the TCM nursing pathway for T2DM. Nurses coordinate with relevant departments promptly to complete necessary examinations. The control group receives routine care.

If there are any changes in the patient’s condition, the responsible nurse promptly analyzes and addresses the changes, adjusting the sequence of items in the TCM nursing pathway as necessary. The head nurse checks the implementation of the TCM nursing pathway for T2DM and the routine care plan daily. The head nurse ensures compliance with the nursing pathway protocol and evaluates the quality of care promptly. Relevant data are collected and evaluated at the time of the patient’s discharge.

#### Sample Size Calculation

A literature-based approach was used to compare the preset effect, with α=.05 and β=.10, against the known efficacy of general nursing from previous studies. Based on methods found in the literature [10] and conclusions from earlier research, the historical effective rate (very satisfied + satisfied) was determined to be approximately 74.5% [9]. The effective rate for this pathway nursing program is projected to be 85%. Using *Z* values from standard tables (*Z*1 – α / 2 = 1.96; *Z*1 – β = 1.28), the sample size for each group was estimated as follows:

N1 = N2 = (*Z*1 – α / 2 + *Z*1 – β) 2 [P1(1 – P1) + P2(1 – P2)] / δ2 = (1.96 + 1.28) 2 [0.745 × (1 – 0.745) + 0.85 × (1 – 0.85)] / (0.85 – 0.745) 2 = 296. Thus, 242,272 indicated 297 cases, and the sample size of this study was 297 × 2 = 594 cases.

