**Methods:**

This study uses a prospective, randomized, single-blind, parallel-controlled design. Based on sample size calculations, the study will include 594 patients with diabetes, with 2 groups of 297 patients: an observation group will receive a TCM nursing program based on clinical pathways, while a control group will receive routine care. Both groups will be evaluated before and after the intervention using assessment indicators. The primary outcome is the quality of life score, measured by a diabetes-specific quality of life questionnaire. Secondary outcomes include hospital stay duration, medical expenses, health knowledge, blood glucose control, symptom scores, and patient satisfaction.

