#### Randomization Method

The randomization method used in this study involves selecting an appropriate block size and assigning participants into 2 groups (the study group and the control group) in a 1:1 ratio. Using the *PROC PLAN* procedure statement in SAS (version 9.2; SAS Institute) and specifying a seed number, a randomized allocation was generated for 594 participants. This process produced a complete randomization table, listing the treatment assignments corresponding to sequential serial numbers from 001 to 594.

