#### Outcomes

Researchers use standardized questionnaires to collect baseline data. The primary efficacy indicator is a quality of life scale (the Diabetes-Specific Quality of Life Scale) [11]. Secondary efficacy indicators include the length of hospital stay, medical costs, blood glucose control, patient symptom scores, patient satisfaction, and the level of health knowledge acquired at admission. Data are collected 1 day before discharge and at 4 weeks, 12 weeks, and 24 weeks after discharge.

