### Statistical Analysis

We will use SPSS (version 26.0; IBM Corp) to perform the statistical analysis. Descriptive statistics for quantitative variables will include at least the mean and SD or the median and IQR. Descriptive statistics for qualitative variables will include at least the frequency and percentage for each category. Comparisons between the 2 groups will be conducted using an independent-sample *t* test (for normally distributed data with equal variances) or the nonparametric rank-sum test. For unordered categorical data, comparisons between the 2 groups will be made using the *χ*^2^ test or Fisher exact test, while ordinal categorical data will be analyzed using nonparametric tests. All statistical tests will be 2-sided, with a *P*<.05 considered statistically significant.

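### The only sample size calculation is for patient satisfaction, a secondary outcome, so its 90% power does not apply to the primary quality-of-life score, whose power is unstated

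*Protocol article*

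**What the plan says.** The Abstract (Methods) states: "The primary outcome is the quality of life score, measured by a diabetes-specific quality of life questionnaire". The Outcomes section agrees: "The primary efficacy indicator is a quality of life scale (the Diabetes-Specific Quality of Life Scale"). Both places list patient satisfaction among the secondary outcomes.

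The Sample Size Calculation section uses a different variable. It works "with α=.05 and β=.10" from a historical figure: "the historical effective rate (very satisfied + satisfied) was determined to be approximately 74.5" percent. For the new programme, "The effective rate for this pathway nursing program is projected to be 85" percent. These two proportions go into an unpooled two-proportion formula, and the section concludes that "the sample size of this study was 297 × 2 = 594 cases". No other sample size or power statement appears in the article.

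The Statistical Analysis section compares quantitative variables by an independent-sample t test or a rank-sum test, and states: "All statistical tests will be 2-sided".

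**The concern.** The parenthesis in the sample size text identifies the rate as patient satisfaction. The trial is therefore sized on a binary secondary outcome, while its primary outcome is a score to be analysed by a different kind of test. No quality-of-life difference, SD or responder definition is given, and nothing links the satisfaction rate to the quality-of-life score.

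At stake is the justification of the sample size. A reader who sees a total of 594 and beta of .10 will naturally take them as the design power for the primary question. The article supports them only for satisfaction. For quality of life it states neither the effect the trial was meant to detect nor the chance of detecting it.

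**Working it through.** **Inputs.** From the Sample Size Calculation section: rates 0.745 and 0.85, Z values 1.96 and 1.28, 297 per group. From Randomization Method: 1:1 allocation. From Statistical Analysis: two-sided tests at .05, and a t test for a normally distributed score. From Results: 101 randomized per group to date. The article gives no quality-of-life SD or important difference, so results for the primary are in SD units over an assumed range.

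**1. The plan's own figure.**

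- Variance term: 0.745 × 0.255 + 0.85 × 0.15 = 0.189975 + 0.1275 = 0.317475.
- n per group = (1.96 + 1.28)² × 0.317475 / 0.105² = 10.4976 × 0.317475 / 0.011025 = 302.3, so 303.
- The printed result is 297, about 2% lower. Power for satisfaction at 297 per group, same unpooled variance: Φ(0.105 / √(0.317475/297) − 1.96) = Φ(3.21 − 1.96) = 89.5%.

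The calculation is thus essentially reproduced, apart from a small slip, and the result confirms that the 90% belongs to satisfaction.

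**2. What 297 per group gives for a continuous score** (normal approximation, no losses).

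- Detectable difference at 90% power: (1.960 + 1.2816) × √(2/297) = 0.266 SD.
- Detectable difference at 80% power: (1.960 + 0.8416) × √(2/297) = 0.230 SD.
- Power at difference d (in SD) is Φ(d × √(297/2) − 1.96):

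| Assumed true difference (SD) | Power at 297 per group | n per group for 90% power |
|---|---|---|
| 0.10 | 23% | 2102 |
| 0.15 | 45% | 934 |
| 0.20 | 68% | 526 |
| 0.25 | 86% | 337 |
| 0.30 | 95.5% | 234 |
| 0.40 | 99.8% | 132 |

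Between 0.20 and 0.40 SD the requirement runs from well above 297 to less than half of it. Nothing in the article places the trial within this range.

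**3. Sensitivity to the evaluable number.** The calculation has no allowance for loss, although there are elimination criteria and follow-up runs to 24 weeks after discharge.

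- Assumed 10% loss (267 per group): power 64% at 0.20 SD, 82% at 0.25 SD, 93% at 0.30 SD.
- Assumed 20% loss (237 per group): 59%, 78% and 90%.
- If only the 101 per group reported so far were analysed, 90% power would need 3.2416 × √(2/101) = 0.46 SD, and power at 0.266 SD would be Φ(0.266 × √(101/2) − 1.96), about 47%.

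**The case against.** The strongest reply is that no loss of power has been shown. With 297 per group, a difference of 0.30 SD would be detected with 95.5% power, and nothing in the article says that effects of 0.10 to 0.20 SD, where power is low, are the relevant ones. This stands. A reader might infer that the trial is underpowered for quality of life, but the documents do not support that. They show only that power for the primary is unstated.

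Second, the article nowhere claims 90% power for quality of life; it attaches beta of .10 openly to the satisfaction rate. That is also right. The fault is a mismatch between the sizing outcome and the primary outcome, not a false statement about the primary.

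Third, a reader might infer that a null quality-of-life result would be uninterpretable. That goes too far. A completed trial is read from its confidence interval, and at full enrolment the 95% half-width is about 1.96 × √(2/297) = 0.16 SD, narrow enough to exclude moderate effects. What is missing is a prespecified important difference to set the interval against.

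Fourth, an unseen analysis plan might contain a quality-of-life calculation. It could add one, but this article prints a complete calculation and presents its result as the basis of the trial's sample size, so the mismatch would remain.

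Finally, the Results and Principal Findings sections describe the main aim as comparing health knowledge and scores, which blurs what is primary. This does not rescue the calculation, since health knowledge is not satisfaction either, but it should be settled when the paragraph is rewritten.

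**Conclusion.** The point holds as a mismatch. The stated 594 and 90% power describe a secondary binary outcome and are not a property of the primary comparison. For quality of life, 297 evaluable per group gives 90% power at 0.27 SD and 80% at 0.23 SD. Whether that is enough cannot be judged from the article. These figures assume a two-sided t test at .05, equal groups, no losses and no baseline adjustment. The arithmetic slip in the satisfaction calculation (297 printed, 303 from the stated inputs) is minor and does not affect the conclusion.

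**What to change.** Revise the Sample Size Calculation section as follows.

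- Label the 74.5% versus 85% calculation as applying to the secondary satisfaction outcome, and correct it: the stated inputs give 302.3, so 303 per group, and 297 per group gives about 89.5% power.
- Add for the primary outcome: *With 297 evaluable patients per group and a two-sided t test at .05, the trial has 90% power for a true quality-of-life difference of 0.27 SD and 80% for 0.23 SD; power is 68% at 0.20 SD.*
- Convert these differences to scale points with the pooled baseline SD of patients already randomized, computed without group labels. This reveals nothing about the treatment effect.
- Set the result against a justified important difference at a named primary time point. The Outcomes section lists four collection times and does not say which is primary.
- Restate the power for the number realistically evaluable; for example, 101 per group gives 90% power only at about 0.46 SD.
- Do not quote a smaller detectable difference based on baseline adjustment unless that analysis is adopted. The Statistical Analysis section plans none, and the article gives no baseline correlation.

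The cost is one paragraph, one pooled SD and a justified difference. The planned total need not change. The stated power may look less favourable than the present 90%.

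### The sample-size expression is miscalculated: its own inputs give 302.3 (303 per group, 606 in total), not 296, 297 and 594; the effect on power is small, about 89.5% instead of 90%

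*Protocol article*

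**What the plan says.** The Sample Size Calculation section sets the error rates: "A literature-based approach was used to compare the preset effect, with α=.05 and β=.10". The outcome behind the calculation is satisfaction: "the historical effective rate (very satisfied + satisfied) was determined to be approximately 74.5% [9"]. For the new programme, "The effective rate for this pathway nursing program is projected to be 85" per cent. The section then prints the unpooled formula for two proportions with normal quantiles 1.96 and 1.28, puts the two rates and their difference in, and gives the result as 296. The next sentence reads "Thus, 242,272 indicated 297 cases, and the sample size of this study was 297" × 2 = 594. The integer 296 and the digits 242,272 appear to be one number, 296.242272, split in typesetting and then rounded up to 297.

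The figure recurs elsewhere. The Abstract (Methods) says "the study will include 594 patients with diabetes, with 2 groups of 297 patients", and the Randomization Method section describes an allocation list generated for 594 participants with serial numbers 001 to 594. The Statistical Analysis section confirms two-sided testing: "All statistical tests will be 2-sided, with a *P*<.05 considered statistically significant".

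**The concern.** Every input to the formula is printed, so a reader can evaluate it, and the result is not the one stated. A planned number that does not follow from its own formula cannot be cited as giving the stated beta of 0.10. The sentence carrying the result also makes no sense as printed.

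The section stops at the rounded formula result. The number required is therefore also the number randomized, with no margin. Yet the elimination criteria in Textbox 1 remove some patients after entry, and the Ethical Considerations section allows withdrawal at any time.

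**Working it through.** **Inputs** (Sample Size Calculation, protocol article): quantiles 1.96 and 1.28; P1 = 0.745; P2 = 0.85; difference 0.85 − 0.745 = 0.105. Allocation is 1:1 (Randomization Method).

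**Step 1: the plan's own figure.**
- Numerator: (1.96 + 1.28)² × [0.745 × 0.255 + 0.85 × 0.15] = 10.4976 × (0.189975 + 0.1275) = 10.4976 × 0.317475 = 3.33272556.
- With 0.01125 as the denominator: 3.33272556 / 0.01125 = 296.242272. This matches the printed digits to all six decimals.

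**Step 2: the expression as printed.**
- Denominator: 0.105² = 0.011025, not 0.01125.
- Result: 3.33272556 / 0.011025 = 302.29, so 303 per group and 606 in total.
- Difference from the plan: 303 − 297 = 6 per group, 12 in total; 6 / 297 = 2.0%.

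**Step 3: could another method explain 296?** With the same rates, alpha 0.05 and 90% power:

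| Variant | Per group |
|---|---|
| Unpooled, unrounded normal quantiles | 302.6 (303) |
| Arcsine | 303.1 (304) |
| Pooled variance under the null | 306 |
| Pooled with continuity correction | 325 |
| Pooled, one-sided | 250 |

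None gives 296.

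**Step 4: power at 297 per group, complete data.**
- Unpooled: standard error = √(0.317475 / 297) = 0.032695; 0.105 / 0.032695 = 3.2115; 3.2115 − 1.96 = 1.2515; power = Φ(1.2515) = 89.5%.
- Pooled: mean rate 0.7975; √(2 × 0.7975 × 0.2025) = 0.56832; √0.317475 = 0.56345; (0.105 × √297 − 1.96 × 0.56832) / 0.56345 = 1.2346; power = Φ(1.2346) = 89.2%.
- For comparison, 303 per group gives 90.04% unpooled and 89.7% pooled.

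**Step 5: illustration of loss.** The document gives no loss rate, so these rates are assumptions.
- 10% loss: 297 × 0.9 ≈ 267 per group, about 86% power.
- 20% loss: 297 × 0.8 ≈ 238 per group, about 82% power.

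**The case against.** The strongest reply is that the slip changes almost nothing. Six patients per group is 2% of the planned number, and the power lost with complete data is under one percentage point. The inputs are no more precise than that: the control rate is called approximate and the pathway rate is a projection. With P1 = 0.744 instead of 0.745, the same formula gives 10.4976 × 0.317964 / 0.011236 = 297.1. Even 303 per group falls just short of 90% under a pooled test. All of this stands, and it limits the consequence. It does not make the printed equation true.

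A reader might infer that the trial is materially underpowered, or that the error takes power down to about 82%. The documents support neither. The figures for 10% and 20% loss rest on assumed rates and do not follow from the slip; the same losses would lower power from 303 as well. Nor is it clear that satisfaction is exposed to 24 weeks of follow-up. The Outcomes section gives one collection schedule for all indicators, from the day before discharge to 24 weeks after it, without saying when satisfaction is compared. The section on implementing the pathway refers to data collected and evaluated at discharge. What remains is that the calculation has no allowance for loss or elimination, so 89.5% applies to complete data only.

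A reader might also infer that recruitment must rise to 606. That would change the Abstract and the allocation list for a gain of about half a point of power, and the size of the error does not call for it.

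**Conclusion.** The arithmetic error is certain: the printed expression equals 302.29, not 296.24. Its source, 0.01125 entered for 0.011025, is an inference, because no intermediate step is printed, but the six-decimal match leaves little doubt. The stated 90% is missed only marginally: 89.5% unpooled or 89.2% pooled, a shortfall of about 0.5 to 0.8 points. This assumes 74.5% versus 85% satisfied, two-sided alpha 0.05, 297 analysed per group and no losses.

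The result concerns satisfaction, which the Abstract and the Outcomes section list as secondary. Neither 594 nor 606 shows the power for the primary outcome, the quality of life score, and correcting this line does not alter that.

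**What to change.** In the Sample Size Calculation section, replace the result and the garbled sentence after it with the correct evaluation: 302.3, that is 303 per group. Keep the 594 in the existing randomization list, and add that 297 per group gives about 89.5% power (unpooled; 89.2% pooled) to detect 74.5% versus 85% for satisfaction, a secondary outcome, with complete data, and less with any loss or elimination. If a loss-adjusted figure is added, give its loss rate and label it as an assumption.

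The cost is a text correction in one section and a slightly less favourable power statement. The Abstract's 594 and the allocation list stay as they are, and no extra patients are needed.

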#### Randomization Method

The randomization method used in this study involves selecting an appropriate block size and assigning participants into 2 groups (the study group and the control group) in a 1:1 ratio. Using the *PROC PLAN* procedure statement in SAS (version 9.2; SAS Institute) and specifying a seed number, a randomized allocation was generated for 594 participants. This process produced a complete randomization table, listing the treatment assignments corresponding to sequential serial numbers from 001 to 594.

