**Elimination criteria**
Patients whose condition worsens, resulting in a hospitalization duration exceeding 14 days and increased hospitalization costs.Patients with concomitant systemic diseases that require special treatment, leading to a hospitalization duration exceeding 14 days and increased costs.Patients with serious complications that arise during the course of treatment and necessitate discontinuation of the nursing pathway.Patient and family preferences and wishes that affect the implementation of this nursing pathway.

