### Ethical Considerations

The ethical principles guiding this study include the Measures for Ethical Review of Biomedical Research Involving Humans, Good Clinical Practice for Drug Trials, Regulations on Clinical Trials of Medical Devices, Ethical Review Guidance for Drug Clinical Trials, Clinical Ethical Review Management Guidelines for Traditional Chinese Medicine Hospitals, the Declaration of Helsinki, and the International Ethical Guidelines for Biomedical Research Involving Human Subjects.

The trial has been approved by the Ethics Committee of Guang’anmen Hospital, China Academy of Chinese Medical Sciences (2022-022-KY-01). Prior to the implementation of the study, informed consent must be obtained from patients. Participation in this study is entirely voluntary. Patients may choose not to participate or withdraw from the study at any time without providing a reason, and participation requires signing an informed consent form.

All patient data collected during the trial will remain confidential. Medical records will be identified using research ID numbers instead of names. Identifiable information will not be disclosed to anyone outside the research team unless the patient provides explicit permission.

In accordance with relevant national regulations, in the event of research-related injuries, the study institution, Guang’anmen Hospital of the China Academy of Chinese Medical Sciences, will bear the corresponding medical costs and provide appropriate financial compensation.

For any questions regarding participant rights in this study, individuals can contact the Ethics Committee of Guang’anmen Hospital, China Academy of Chinese Medical Sciences.

The study form will be kept by the data collector in a folder in the study office. Study data will be processed without participants being recognizable. Only the researcher responsible for the analysis can access the final data set; after the trial study is published, we will provide research references and the scientific basis for relevant clinical practice, formulate the implementation specifications of the nursing program under the chosen pathway, and promote the research results in the industry.

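### The 594 patients to be randomized equal the plan's own calculated requirement, so the stated β of .10 for the satisfaction rate presumes that no patient is lost

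*Protocol article*

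**What the plan says.** The Sample Size Calculation section sets its error rates "with α=.05 and β=.10" and takes its control rate from satisfaction with general nursing: "the historical effective rate (very satisfied + satisfied) was determined to be approximately 74.5" per cent. The projected rate under the pathway is 85%. The formula result is rounded up to 297 per group and doubled: "the sample size of this study was 297 × 2 = 594 cases". No step lies between the formula and that total.

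The Randomization Method section describes a 1:1 list of the same length, "listing the treatment assignments corresponding to sequential serial numbers from 001 to 594". The Abstract repeats 594 as two groups of 297.

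The same article provides for loss in three places:
- Elimination criteria (Textbox 1) include a stay beyond 14 days after worsening, the wishes of patient or family, and "Patients with serious complications that arise during the course of treatment and necessitate discontinuation of the nursing pathway".
- Ethical Considerations: "Patients may choose not to participate or withdraw from the study at any time without providing a reason".
- Outcomes: "Data are collected 1 day before discharge and at 4 weeks, 12 weeks, and 24 weeks after discharge".

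The Outcomes section names the Diabetes-Specific Quality of Life Scale as primary and lists satisfaction among the secondary indicators.

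**The concern.** A two-proportion formula returns the number of patients who must contribute an outcome. Using that number unchanged as the number randomized delivers the stated power only if every allocated patient contributes. The article's own rules make that unlikely. The Intervention Plan section places allocation at admission, whereas a long stay or a complication during treatment can be known only later.

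At stake is how a null result would be read. A reader told that β is .10 would take the chance of missing the planned difference in satisfaction to be one in ten, when with ordinary losses it would be larger.

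**Working it through.** **Inputs from the article.** P1 = 0.745, P2 = 0.85, Z = 1.96 and 1.28, 297 per group (Sample Size Calculation). Two-sided testing at .05 (Statistical Analysis: "All statistical tests will be 2-sided, with a *P*<.05 considered statistically significant"). Allocation 1:1 and 594 randomized (Randomization Method). Loss rate: not given, so 5% to 20% is assumed, equal in both groups.

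**Step 1: the plan's own figure.** The printed formula is n = (1.96 + 1.28)² × [P1(1 − P1) + P2(1 − P2)] / δ².
- Variance sum: 0.745 × 0.255 + 0.85 × 0.15 = 0.189975 + 0.1275 = 0.317475.
- Numerator: 3.24² × 0.317475 = 10.4976 × 0.317475 = 3.33273.
- δ² = 0.105² = 0.011025.
- n = 3.33273 / 0.011025 = 302.29, so 303 per group, 606 in total.

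The article prints 296 followed by the digits 242,272. A result of 296.242272 is what the formula gives if δ² is entered as 0.01125 instead of 0.011025. The stated 297 is therefore 6 per group below what the printed inputs require. It holds no hidden reserve for loss.

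**Step 2: power at the number with data.** With n patients per group supplying data, power = Φ(0.105 / √(0.317475 / n) − 1.96). At n = 297, √(0.317475 / 297) = 0.03270, 0.105 / 0.03270 = 3.21, and Φ(1.25) is about 0.895. With n = 297 × (1 − loss), rounded down:

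| Assumed loss | n per group | Power | Chance of missing the planned difference |
|---|---|---|---|
| 0% | 297 | 89.5% | 10.5% |
| 5% | 282 | 87.9% | 12.1% |
| 10% | 267 | 86.1% | 13.9% |
| 15% | 252 | 84.1% | 15.9% |
| 20% | 237 | 81.8% | 18.2% |

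The pooled-variance version gives 89.2%, 87.5%, 85.7%, 83.7% and 81.4%, so the choice of formula moves the answer by at most half a point. Power passes below 80% at roughly 24% loss.

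**Step 3: what an allowance would have required.** Dividing by (1 − loss), the stated 297 becomes 330 per group (660 in total) at 10% loss and 372 (744) at 20%. From 303 the figures are 337 (674) and 379 (758).

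**The case against.** Several points on the other side have force.

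- **The endpoint.** The calculation is for satisfaction, not for the primary quality of life score. A reader might infer that the shortfall applies to the trial whatever the endpoint. The article does not support that. For a continuous score, n = 2 × 3.24² / d² per group, where d is the standardized difference. If d were 0.30, 234 per group would suffice and 594 would absorb about 21% loss. If d were 0.25, 336 would be needed before any loss. Both values are illustrations only. This stands.
- **The time point.** A reader might infer that 594 assumes complete data at every visit to 24 weeks. The Sample Size Calculation section names no time point. If satisfaction is analysed only at the visit before discharge, losses after discharge do not touch this calculation. Elimination and withdrawal during the stay still do. This stands too.
- **Replacement.** A reader might infer from the fixed list that removed patients would be replaced under their old serial numbers. The article mentions no replacement, and a list can be extended with new numbers. No such practice should be attributed to the plan.
- **Analysis sets.** The article does not say whether eliminated patients' data leave the analysis, and a full protocol or SAP may settle it. If those data are kept, the loss is smaller. The point here is narrower than a missing rule: the calculation is shown from inputs to total, and the list length is fixed at that total.
- **Size.** The loss rates are assumed, and power stays above 80% up to roughly 24% loss. That makes the erosion moderate, but β = .10 remains a figure the plan states and does not deliver.

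**Conclusion.** The point holds for the power the article states, which is power for the satisfaction rate. The number randomized equals the number the article gives as its requirement, with no allowance for loss, while its own rules provide for elimination after allocation and for withdrawal. On the printed inputs β = .10 is narrowly missed even with no loss (89.5%). At an assumed loss of 10% to 20%, power is about 86% to 82%, and the chance of missing the planned difference is about 14% to 18%.

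These figures assume the planned rates of 74.5% and 85%, equal loss in the two groups, all 594 randomized, and lost patients supplying no satisfaction outcome. The loss that counts depends on when satisfaction is analysed. Nothing quantitative can be said about power for the primary outcome. The matter is worth correcting, but it does not by itself threaten the design.

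**What to change.** Keep 594. In the Sample Size Calculation and Randomization Method sections, state that 594 is the number randomized and not the number expected with data. State the loss assumed, and replace β = .10 with the power at the resulting analysable number, naming the outcome and time point to which it applies. On the current satisfaction inputs that would be about 86% at 10% loss and about 82% at 20%. If the calculation is redone for the quality of life score, apply the same loss allowance there.

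The cost is about two sentences and no extra patients; the price is a less favourable stated power. The Abstract reports that no statistical analysis has yet been conducted, so the change can still be made without knowledge of the results. Enlarging the trial to the totals in step 3 would also restore 90%, but at far greater cost and for a secondary outcome.
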